### 2.6. Study Variables

The variables that will be collected are listed in Table 1.

Comorbidity will be assessed using the Cumulative Illness Rating Scale (CIRS), a validated tool used for hospitalized geriatric patients [14]. The disease severity score, ranging from 0 to 4, is based on 14 components reflecting organs impacted by a chronic disease. The CIRS Severity Index measures the number of items with disease severity ratings of three or four. This index is measured on hospital discharge forms at a national level.

To assess the complexity of patients, the score of the Corridor Triage (Tri-Co) instrument will be collected. Tri-Co is composed of the Modified Early Warning Score (MEWS) [15] and the Index of Care Dependency (IDA) [16]. The first tool collects data on clinical stability/instability, while the second one classifies information on care complexity. The integration of those two instruments is justified by the concept that clinical instability and care complexity should naturally complement each other to correctly classify patients according to their level of care intensity and ensure that the provision of care is proportional to the patient’s clinical complexity [17]. Tri-Co has been previously evaluated in several Italian settings [18,19,20]. If Tri-Co is not used in the hospital or wards included in this study, considering the expected heterogeneity in care complexity assessment among hospitals, other validated tools for measuring complexity will be considered. For example, the National Early Warning Score (NEWS), the Index of Care Intensity (IIA), or the Index of Care Complexity (ICA) may be considered [20]. All these measures will be collected as single measures at the beginning and at the end of the patient’s stay and specifically at the time of patient’s admission and the last measurement before discharge, as these assessments are made by nurses to ensure adequate nursing planning.

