Moreover, nursing costs will also be compared between patients with chronic and acute diseases. This will allow us to explore the hidden nursing costs derived from the nursing care delivered on an ongoing basis for chronic diseases (e.g., symptom monitoring, administration of medication for the chronic disease, etc.) that did not show signs of exacerbation during hospitalization. A subgroup analysis will be considered to determine which patients require more nursing care (in terms of time and costs). The nursing case mix (i.e., the patient characteristics that best explain the amount and costs of nursing care) will be evaluated to provide evidence for separating out nursing care activities and nursing intensity in the Italian prospective payment system.

To enable accurate data analysis, the need to normalize scores obtained from different rating scales measuring the same outcome will be evaluated. If information from the retrieved nursing records is missing, a missing value analysis will be performed to assess the appropriateness of multiple imputation [21]. Specifically, the reason for missingness will be examined, followed by the analysis of fraction of missing information and assessment of auxiliary variables to be used for multiple imputation. Then, sensitivity analyses involving several imputation models may be performed based on missing value analysis. Patients with missing data from all variables retrieved from the nursing record (i.e., missing data on nursing activities, nursing assessment and patient complexity) will be excluded. All descriptive and inferential analyses will be performed using R V. 4.4.2 [22] or similar software. The level of significance for all analyses will be fixed at *p* < 0.05.

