## Figures and Tables

**Figure 1 healthcare-13-00167-f001:**
[figure not shown]
Study phases.

**Table 1 healthcare-13-00167-t001:** Variables that will be collected divided by data source.

Hospital discharge data	Patient sociodemographic characteristics
	Date of patient admission
	Date of patient discharge
	DRG^†^ number assigned for each admission
	MDC number related to assigned DRG
	Admission diagnosis ^$^
	Discharge diagnosis ^$^
	1st secondary diagnosis ^$^
	CIRS
Nursing record data	Number of nursing activities performed for the same DRG
	Type of nursing activities
	Patient-related care complexity *
	Nursing assessment ^§^

DRG^†^: Diagnosis-Related Group; MDC: Major Diagnostic Category; ^$^: based on the *International Classification of Diseases*, 9th Revision, Clinical Modification (ICD-9-CM); CIRS: Cumulative Illness Rating Scale; ^§^: intended as the assessment carried out on the patient through the use of rating scales according to the company organization; *: care complexity will be measured by means of a validated tool used by hospitals.

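### Only the first secondary diagnosis is collected for a comparison aimed at stable chronic disease, and complexity tools that may differ by hospital or ward are not made comparable by normalization alone

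*Protocol article*

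**What the plan says.** **Chronic versus acute.** Section 2.8 states that "nursing costs will also be compared between patients with chronic and acute diseases". The stated purpose is to expose the hidden cost of ongoing care for chronic disease that shows no exacerbation during the stay. No rule for forming the two groups is given. From the discharge record, Table 1 lists the admission diagnosis, the discharge diagnosis, the "1st secondary diagnosis" and CIRS. Section 2.6 describes CIRS as 14 organ components scored 0 to 4, and its Severity Index as the number of items rated 3 or 4. The next sentence says that this index is on discharge forms nationally.

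**Complexity.** Section 2.6 makes Tri-Co the first-choice tool and explains its two parts, MEWS and IDA: "The first tool collects data on clinical stability/instability, while the second one classifies information on care complexity". Using both is justified because "clinical instability and care complexity should naturally complement each other to correctly classify patients according to their level of care intensity". The fallback applies "If Tri-Co is not used in the hospital or wards included in this study": in that case "the National Early Warning Score (NEWS), the Index of Care Intensity (IIA), or the Index of Care Complexity (ICA) may be considered", named as examples of other validated tools. Section 2.8 plans complexity subgroups. On scores from different scales it says that "the need to normalize scores obtained from different rating scales measuring the same outcome will be evaluated".

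**The concern.** Two measurement choices feed the case-mix results that the study wants to take to the Italian payment system.

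First, the chronic-disease comparison looks for background disease, which may be coded below the first secondary diagnosis. A field that was never extracted cannot be recovered by a later analysis plan. If chronic patients are missed, they sit in the comparison group and pull the two means together.

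Second, section 2.6 argues that instability and care complexity are both needed to classify a patient, then accepts a substitute that may capture only one of them. Section 2.8 offers only a possible normalization. If sites use different tools, a pooled high-complexity subgroup may contain differently defined patients at different sites. Because the tool is set by hospital or ward and each area has one hospital, a tool effect could pass for a hospital or regional effect. Secondary objective 2 intends to control for hospital and region, and secondary objective 3, on care-need differences within a DRG, plausibly draws on these scores.

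**Working it through.** The protocol gives no figure on either issue, so there is nothing to reproduce. The check sets the passages side by side and illustrates the two mechanisms with assumed inputs.

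**1. Can the listed variables find stable chronic disease?**

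- Target: chronic disease without exacerbation during the stay (section 2.8).
- Diagnosis codes: admission, discharge and one secondary diagnosis (Table 1). A stable condition coded second or lower among the secondary diagnoses is not extracted.
- CIRS: the 14 item scores could show chronic disease of any grade. The Severity Index counts only ratings of 3 or 4, so disease rated 1 or 2 adds nothing to it. Table 1 says CIRS without saying whether items or index, and section 2.6 speaks of the index when it mentions discharge forms.

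Effect of missed patients. Let *P* be the true share of chronic patients, *s* the share of them that the rule finds, and assume that no acute patient is wrongly called chronic. The chronic share of the acute group is

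*m* = *P*(1 − *s*) / [*P*(1 − *s*) + (1 − *P*)].

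If missed chronic patients carry the same extra cost *d* as those found, the observed difference is *d*(1 − *m*). With *P* = 0.5 and *s* = 0.5, *m* = 0.25 / 0.75 = 33%. Over a range of assumed values, *m* is:

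| *P* | *s* = 0.3 | *s* = 0.5 | *s* = 0.7 | *s* = 0.9 | *s* = 1 |
|---|---|---|---|---|---|
| 0.3 | 23% | 18% | 11% | 4% | 0% |
| 0.5 | 41% | 33% | 23% | 9% | 0% |
| 0.7 | 62% | 54% | 41% | 19% | 0% |

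Neither *P* nor *s* is in the protocol. The table shows only that the shrinkage equals the misplaced share and that the plausible range is wide. It vanishes when the rule finds every chronic patient. It is smaller if the missed patients, having milder disease, cost less extra than those found.

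**2. Does normalization make different tools comparable?**

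- By section 2.6, MEWS and IDA capture different things, and each complements the other.
- A substitute tool may capture one of them. That NEWS is an instability score is inferred from its name and from the account of MEWS. The protocol does not describe the content of NEWS, IIA or ICA.
- Rescaling changes the units of a score. It does not change how closely the score tracks care complexity.

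Illustration by simulation, with assumed inputs: no true difference between hospitals, scores standardized, and the top third called high complexity. Where the tool correlates 0.8 with true complexity, 72% of the group so labelled is truly in the top third and its mean true complexity is 0.87 SD. Where the correlation is 0.5, the figures are 55% and 0.54 SD. The means scale with the correlation: 0.87 × 0.5 / 0.8 = 0.54. The scores share one scale, but the subgroups are not the same kind of patient.

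**3. Is the tool separable from place?** There are five hospitals, one per area (section 2.3). If the tool differs between hospitals, each tool belongs to particular hospitals and areas. If it differs between wards, it is tied to ward. Pooled data then offer little or no way to tell a tool effect from a site effect.

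**The case against.** The strongest reply is that the protocol commits to less than a critic may read into it.

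- A reader might infer that case mix rests on the first secondary diagnosis alone, so that chronic patients will be counted as acute. The documents do not support that. Admission and discharge diagnoses and CIRS are also collected, no grouping rule is stated, and if CIRS item scores were used there might be no leakage. A missing rule is something an article may leave to the full plan. What stands is the extraction list, which the article does fix, and the doubt whether more than the Severity Index will be available.
- A reader might infer that normalization will wipe out true differences between hospitals. That would follow from standardizing within each hospital, but the protocol names no method and only evaluates the need. Secondary objective 2 also controls for hospital, which would absorb mean shifts in that model.
- The phrase on scales measuring one outcome can be read as a restriction: normalize only where scales share an outcome. It may also refer to the nursing-assessment scales in Table 1. On that reading section 2.8 does not contradict section 2.6, but it then leaves sites whose tools measure different things with no stated way into the pooled subgroups.
- If every ward uses Tri-Co, the second issue does not arise. Section 2.6 itself expects heterogeneity between hospitals.

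**Conclusion.** The point holds as two conditional weaknesses.

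The list of discharge variables is too narrow for a comparison aimed at stable chronic disease. If the groups come from the listed codes or from the Severity Index, some chronic patients risk being placed in the acute group. The contrast then shrinks by the share misplaced, assuming equal extra cost. The documents give no basis for a particular figure.

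If tools differ between sites, normalization does not make pooled complexity subgroups comparable, and tool is confounded with hospital and region, or with ward. This rests on the protocol's own statement that instability and care complexity are distinct, and on an inference about what the substitute tools measure.

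The reach is limited to the subgroup, chronic-versus-acute and case-mix analyses. A reader might extend the criticism to the primary aims, but nursing-cost variability between and within DRGs, and the share of nursing-intensity variability explained by DRGs, need neither the complexity scores nor the chronic flag. The changes are worth making because the case-mix results are meant as evidence for payment policy and the remedy is cheap.

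**What to change.** 1. In Table 1, replace the single secondary diagnosis by all secondary diagnoses on the discharge record, and request CIRS item scores where they exist. State whether CIRS means items or Severity Index.
2. State how chronic disease is identified. Regress nursing cost on the number of chronic conditions within DRG, in place of or alongside the two-group comparison.
3. Reconcile sections 2.6 and 2.8: say which scales are regarded as measuring one outcome. Analyse complexity scores within tool or within hospital, keep instability and care-complexity scores as separate variables, and do not pool across constructs. Hospital-specific cut-points such as tertiles also discard differences between hospitals, so these analyses should be read as within-site results.
4. In pooled models use CIRS plus age as the common case-mix variables. Section 2.6 describes CIRS as validated in hospitalized geriatric patients whereas all adults are eligible, so its use in younger patients should be noted as a limitation.

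The cost is a few more extracted columns from a record already being read, some rewording of the analysis section, and complexity results that pool less readily across sites. The primary analyses do not change.

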### 2.9. Source of Bias

The potential sources of bias in this study will include selection bias due to the proposed convenience sample, which will consist of five public hospitals in Italy. However, we expect to collect a substantial amount of data from patients across all geographical areas of Italy, with an estimated sample size of at least 15,000 individuals. Data collection bias may also arise from retrospective data collection, where incomplete records could affect the results, leading to inconsistencies in estimating the amount of nursing activities digitally registered and the related nursing costs. This bias will be controlled by performing multiple data imputation. Contextual biases related to institutional policies and healthcare culture may also influence nursing practices and patient care across different hospitals. Therefore, a thorough examination of institutional policies and healthcare cultures will be required to address contextual biases during data analysis. A potential source of bias is that the estimated nursing costs are based on a convenience sample of nurse estimates. This approach may not accurately capture the variability in nursing care across different settings. As a result, there is a risk of either overestimating or underestimating nursing costs, depending on how accurately nurses report the time spent on various activities. Thus, the development of standardized data collection guidelines, and the provision of comprehensive training for staff, will be essential to ensure consistency and accuracy in records, thereby minimizing measurement bias related to the reporting of nursing activity time. Finally, the implementation of ongoing evaluation and feedback mechanisms will further help identify and correct biases throughout the research process.

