### 2.7. Procedures

This study started in January 2024 and is planned to end in March 2025. First, a pilot study was conducted to assess the characteristics of the EHR in the enrolled hospitals. Given the lack of a unique national electronic system for storing health information, heterogeneity in the collection and organization of the nursing activities is expected. Therefore, a preliminary meeting was organized with the nursing directors of each hospital. During this meeting, nursing directors described the EHR used in their hospitals. From this information, an electronic dataset was prepared to allow each hospital to enter information on nursing care activities. For each hospital, two medical and two surgical wards will be considered for enrolment. If there are more than two medical/surgical wards in the same department, the two wards with the highest number of patients admitted during the study period will be selected.

Eligible patients will be enrolled by searching the EHR. Data will be collected retrospectively to gather information on nursing care provided in 2022. This study will collect data from all patients included in medical or surgical DRGs. All nursing activities performed on these patients and documented in the EHR will be considered.

Within each hospital, a procedural manager will be designated to extract and de-identify data of interest. The data of patients who meet the inclusion criteria will be transmitted to the principal investigator (PI) by uploading the data into a secure server specific for this study. The upload will take place via a dedicated cloud platform established on an ad hoc basis for the project, allowing each local investigator of the participating centers to access and provide data.

For login purposes, each local investigator will have a username and password (which can be modified by the user after the initial login). Each local investigator will only have access to his or her own uploaded data, while the principal investigator will have access to all the data submitted by each participating center. The Italian Regulatory Board for Nursing Professions (FNOPI) owns the server where the data will be kept. Data gathering will be continuously evaluated, and all disaster recovery measures will be in place. Figure 1 summarizes the steps of the study.

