### 2.8. Data Analysis

Descriptive statistics (frequency, percentage, mean, median, range, and standard deviation) will be used to describe the sample. *t*-tests, ANOVA (or related nonparametric tests in case of a non-normal distribution of dependent variables), linear regression, and quantile regression will be performed to evaluate the possible variability in nursing time across hospitals and DRGs.

The chi-square test will be used to analyze any differences in the average frequency of nursing activities within the same DRG. In addition, we will perform linear, logistic and quantile regression, considering cost as the outcome of nursing care. Nursing costs will be assessed across hospitals and DRGs. The quantile regression will be used to explore which factors are associated with the different quantiles of nursing costs.

Nursing costs will be calculated based on several factors, including the average time required to perform each procedure, nurses’ hourly wage, the cost of materials used, and the average length of patient stay. Nursing time will be estimated using a convenience sample of nurses from the hospitals included in this study. For each nursing activity, the participating nurses will indicate the average time spent on the activity and devices relevant to each intervention. Nursing costs will be calculated by applying nurses’ salaries, based on national cost tables for nursing professionals. The annual nursing salary will be used to estimate the cost per minute of nursing time. This cost per minute will then be multiplied by the amount of time spent on each nursing activity and by the total number of activities performed for each patient. Additionally, the cost of devices required to perform each activity will be included, based on prices from the national price list. Thus, the cost per patient per day of hospitalization will be calculated. This cost will enable us to compare patients with different lengths of stay. Finally, subgroups based on patient complexity will be considered.

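### Multiple imputation cannot control the bias from uncharted nursing activities: an uncharted activity lowers an observed count and leaves no missing value

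*Protocol article*

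**What the plan says.** Section 2.9 warns that "incomplete records could affect the results, leading to inconsistencies in estimating the amount of nursing activities digitally registered and the related nursing costs", and continues: "This bias will be controlled by performing multiple data imputation". No condition is attached.

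The outcome is defined elsewhere. Section 2.7: "All nursing activities performed on these patients and documented in the EHR will be considered". Table 1 lists the variable as "Number of nursing activities performed for the same DRG". Section 2.8 obtains cost from a cost per minute "multiplied by the amount of time spent on each nursing activity and by the total number of activities performed for each patient", and adds the devices used.

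On differences between sites, Section 2.7 says that "heterogeneity in the collection and organization of the nursing activities is expected", and Section 3 lists the differing record systems as a limitation. Section 2.8 nevertheless plans to compare nursing time and cost across hospitals as well as across DRGs. Adjustment for hospital is named only in secondary objective 2 (Section 2.1).

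On imputation, Section 2.8 is more cautious than Section 2.9. Missingness is examined first, to judge whether imputation is appropriate, and only patients with nothing at all from the nursing record are excluded. Section 3 says only that imputation will be considered.

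**The concern.** Imputation fills values that are known to be missing. Under-charting does not produce such values: the patient keeps a count, and the count is too low. The missingness review in Section 2.8 cannot detect this, and the exclusion rule keeps a partly charted patient in the analysis with the low count taken at face value.

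Both primary aims use this outcome: the variability of nursing cost between and within DRGs, and the share of variability in nursing intensity that DRGs explain. If hospitals chart different shares of the care they give, that difference enters the within-DRG variability and dilutes the share explained by DRG. With one hospital per geographical area (Section 2.3), charting practice, hospital and area also coincide. The results are meant to inform the payment system (Section 2.8) and to go to government authorities (Section 4), so a statement that this bias is controlled will carry weight.

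**Working it through.** **1. Nothing to reproduce.** The sentence in Section 2.9 rests on no figure. The expected 15,000 patients in the same section come with no effect size or capture rate.

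**2. What incompleteness does to the outcome.** Let N be the activities done for a patient, R the activities charted, and p the share that the hospital captures, so that E(R) = p × N. Cost is a sum over activities of (cost per minute × minutes + devices) × R. If p is the same for all activity types in a hospital, expected recorded cost = p × true cost.

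**3. What imputation can act on.**
- *Activity done but not charted:* R is observed and too low. There is no missing value, and imputation leaves it unchanged.
- *Activity type that a hospital's system does not hold:* it may appear as a blank in the common dataset described in Section 2.7. Imputation can then run, but that hospital supplies no information on its own level, which can only be borrowed from the other hospitals.
- *Blank complexity score, assessment or discharge variable:* an ordinary missing value, where imputation is legitimate.

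The Section 2.9 sentence is about the amount of registered activity and its cost, that is, the first two cases.

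**4. Simple size (capture rates assumed).** Identical care, capture 90% and 60%: 0.60/0.90 = 0.667, so recorded cost is 33% lower. Capture 100% and 60%: 1.00/0.60 = 1.67-fold.

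**5. Effect on the primary aims (simulation, all inputs assumed except the total).** Five hospitals × 3,000 = 15,000 patients (equal split assumed); 20 DRGs spread evenly, with means of 15 to 35 activities per day; 8 minutes per activity at 0.40 per minute; identical true care in all hospitals; each activity charted with the hospital's capture probability. No missing values arise.

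| Capture in the five hospitals | True mean cost per day | Recorded mean cost per day | Variance explained by DRG, true / recorded | Between-hospital share of within-DRG variance, true / recorded |
|---|---|---|---|---|
| 90% in all | 78.8 to 80.6 | 70.8 to 72.6 | 0.286 / 0.281 | 0.005 / 0.005 |
| 95% down to 85% | 78.3 to 80.7 | 76.6 to 68.3 | 0.285 / 0.278 | 0.007 / 0.016 |
| 95% down to 65% | 80.0 to 80.7 | 76.1 to 52.1 | 0.280 / 0.245 | 0.005 / 0.107 |

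The ANOVA across hospitals on recorded cost gave p = 0.24, about 4e-23 and below 1e-200. On true cost it gave 0.31, 0.031 (chance, since true care was generated identically) and 0.91.

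**6. What within-hospital estimation recovers.** In the last row, hospital takes 0.073 of recorded variance. DRGs are evenly spread over hospitals here, so the share explained by DRG within hospital is about 0.245/(1 − 0.073) = 0.264. That is closer to the true 0.280, but not equal to it.

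**7. Sample size does not protect.** With 3,000 patients per hospital and two-sided alpha 0.05, the standard error of a difference, relative to the mean, is CV × √(2/3000) = 0.0258 × CV. A purely documentary 5% gap is then declared significant with probability above 0.99 at CV 0.3, 0.97 at CV 0.5 and 0.49 at CV 1.0. A 10% gap gives at least 0.97 throughout.

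**The case against.** The best reply is that Section 2.9 is loose wording, and that the operative text is Section 2.8, which examines why data are missing before deciding on imputation and allows sensitivity analyses under several imputation models. Section 3 openly lists differing record systems as a limitation. This shows that the protocol is more careful elsewhere, but it does not rescue the sentence: each of those steps concerns values known to be missing.

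Four stronger readings are tempting, and the document does not support them.

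- *Imputation has nothing at all to act on.* Too absolute. Section 2.8 itself mentions missing activity data, and an activity type that a system lacks may show as a blank.
- *Capture that differs by hospital breaks missing at random.* Hospital is observed for every patient, so dependence on hospital alone would not break it. The difficulty is that under-charting is not flagged.
- *Training is offered as a cure for poor 2022 charting.* The words "will be essential to ensure consistency and accuracy in records" might suggest it, but the same sentence ties the measure to bias in reported activity times, which nurses supply by estimate.
- *Charting differences will be reported as differences in care, and are the main bias.* No capture rate is given, and the error in nurses' time estimates enters the same cost product. The supportable statement is that the two cannot be told apart.

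Adjustment for hospital can absorb much of a hospital-wide shift when DRGs are compared. It is planned only for one secondary objective, and it does not help a comparison between hospitals.

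**Conclusion.** The concern holds in this form: the statement that multiple imputation will control the bias is wrong for activities done but not charted, and it goes further than Sections 2.8 and 3. For activity types absent from a whole hospital's system, imputation could only import other hospitals' levels. Comparisons of nursing time and cost across hospitals therefore cannot separate documentation from care, and the primary measures of within-DRG variability and of variance explained by DRG are exposed to the same problem.

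The size depends on how far capture differs, which the protocol expects but does not quantify. On assumed capture of 60% to 100% the spurious cost ratio reaches 1.67. In the simulation with capture from 95% to 65%, the variance explained by DRG fell from 0.280 to 0.245, and the between-hospital share of within-DRG variance rose from 0.005 to 0.107. If capture were equal in all hospitals, absolute cost would still be too low, but the comparisons would be almost unaffected (first row of the table).

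**What to change.** 1. Delete the claim of control in Section 2.9. Limit multiple imputation to truly blank fields, such as complexity scores, assessments and discharge variables, in line with the cautious wording of Sections 2.8 and 3.
2. For the primary aims, and not only for secondary objective 2, estimate DRG effects and the variance explained by DRG within hospital, using hospital fixed effects. On a log scale a uniform capture factor is fully absorbed. On the cost scale only the level is, because DRG contrasts are still multiplied by each hospital's capture.
3. Label between-hospital results as differences in recorded activity and in the cost of recorded activity.
4. Add a sensitivity analysis that rescales each hospital's counts over a stated, assumed capture range, for example 60% to 100% (multiplying counts by 1.67 down to 1.00).
5. Add a secondary sensitivity analysis restricted to activity types that all five EHRs record; the pilot described in Section 2.7 should supply the list. Making this list the primary outcome is not required: it would change what is estimated, could drop DRG-specific activities, and would not repair under-charting of the listed items.

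The cost is a little more analysis and a more modest claim, with no new data. Hospital effects do not remove capture that varies by ward, DRG or activity type, and the limitations section should say so.
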